#### **Secondary objectives**

1. To assess the seroprevalence according to vaccination status among NH residents and staff in Belgium at month 0 and at every follow-up visit in the cohort at month 2, 4, 6, 8 and 10.
2. To assess the risk of getting a SARS-CoV-2 infection since vaccination between:
  - Residents and staff
  - Seropositive and seronegative participants at all timepoints
  - Individuals with or without previous self-reported SARS-CoV-2 infections
  - Adjusted for the updated vaccination degree of NH at all timepoints
3. To assess the proportion of confirmed COVID-19 deaths and non-COVID-19 related deaths and the time until death since vaccination (within the study timeframe) between sero-positive and -negative participants for NH residents
4. To assess the duration of SARS-CoV-2 specific antibody responses (seroreversion/no antibody response) since vaccination among NH residents and staff in Belgium.

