Therefore, to assess both the first (seroprevalence) and second (cumulative sero-incidence) research question, the sample size will include 69 NHs, each including 44 participants (20 staff, 24 residents). This brings the total sample size up to 3036 participants.

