### **Secondary objectives**

4. To assess the seroprevalence according to vaccination status among NH residents and staff in Belgium at month 0 and at every follow-up visit in the cohort at month 2, 4, 6, 8 and 10.

The seroprevalence among NH residents and staff in Belgium at month 0, and follow-up in the cohort at month 2 (and if relevant at month 4, 6, 8, and 10), will be reported according to the vaccination status (Number of shots: 0, 1 or 2) and for the subgroups ‘with’ and ‘without’ a history of self-reported SARS-CoV-2 infection, averaged over NHs based on a GEE analysis with exchangeable covariance structure.

5. To assess the risk of getting a SARS-CoV-2 infection since vaccination between:
  - Residents and staff
  - Seropositive and seronegative participants at all timepoints
  - Individuals with or without previous self-reported SARS-CoV-2 infections
  - Adjusted for the updated vaccination degree of NH at all timepoints

For vaccinated participants only, a survival analysis will be performed to investigate the time (in days) to a SARS-CoV-2 infection since vaccination between sero-positive and -negative

participants at all time points. A participant is considered to have an event when the participant had a positive PCR test result (or a positive antigen rapid test, or a positive CT scan, or a positive saliva test in absence of a PCR test). The survival or censoring time (in days) is registered since 14 days after being fully vaccinated (full dose regimen) until first event (or censoring moment). If the proportional hazard assumption holds, a stratified (by NH) Cox proportional hazards regression model will be used to model the hazard of SARS-CoV-2 infection between sero-positive and -negative participants at all time points (modelled by the inclusion of a time-varying seropositivity status), adjusted for type of participant, history of self-reported SARS-COV-2 infections, and a time-varying NH vaccination degree. The analysis will be performed stratified by type of participant or other variables, if the proportional hazard assumption does not hold.

6. To assess the proportion of confirmed COVID-19 deaths and non-COVID-19 related deaths since vaccination and the time until death (within the study timeframe) between sero-positive and -negative participants for NH residents

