### **Tertiary objectives**

Although this study was not designed to assess vaccine effectiveness, end points will be compared between vaccinated and non-vaccinated participants, applying propensity score methods, if sufficient non-vaccinated participants occur in the random selected sample.

8. To assess the risk of getting SARS-CoV-2 infected between vaccinated and non-vaccinated (at last visit) residents/staff.

If a sufficient number of non-vaccinated participants are available in the sample, a survival analysis will be performed to investigate the time (in days) to a SARS-CoV-2 infection

since 14 days after being fully vaccinated between vaccinated and non-vaccinated participants. A participant is considered to have an event when the participant had a reported positive PCR test result (or a positive antigen rapid test, or a positive CT scan, or a positive saliva test in absence of a PCR test) during the baseline or one of the follow-up visits. The survival or censoring time (in days) is registered since 14 days after being fully vaccinated (or since 14 days after main (second) vaccination date in corresponding NH in case of non-vaccinated participants) until first event (or censoring moment).

If the proportional hazard assumption holds, a stratified (by NH) Cox proportional hazards regression model will be used to model the hazard of SARS-CoV-2 infection between staff and residents, and between vaccinated and non-vaccinated participants, adjusting for history of self-reported SARS-COV-2 infections, and a time-varying NH vaccination degree. Propensity score methods will be applied to reduce the effects of confounding. If insufficient non-vaccinated residents would be available in the cohort, the analysis will be performed for staff only.

9. To assess the proportion of confirmed COVID-19 deaths and non-COVID-19 related deaths and the time until death (within the study timeframe) between vaccinated and non-vaccinated residents.

If sufficient non-vaccinated residents would be available, a survival analysis will be performed to investigate the time (in days) to a confirmed COVID-19 death since 14 days after vaccination (or since 14 days after main (second) vaccination date in corresponding NH in case of non-vaccinated participants). A non-COVID-19 related death will be considered as a competing risk in the analysis.

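### If proportional hazards fails and participant type becomes the stratifier, the planned model gives no resident-versus-staff estimate, although objective 5 lists that comparison

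*Protocol*

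**What the plan says.** The secondary objective is worded "To assess the risk of getting a SARS-CoV-2 infection since vaccination between" and is followed by a list that opens with "residents and staff". It goes on to seropositive versus seronegative participants and to those with versus without an earlier self-reported infection. The list stands in Protocol section 2.1 (second secondary objective) and again in section 3.2, where it is numbered 5. Its last entry, the vaccination degree of the home, is an adjustment and not a comparison.

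The analysis in section 3.2 is limited to vaccinated participants. It runs from 14 days after full vaccination to the first diagnosed infection. The model is conditional: "If the proportional hazard assumption holds, a stratified (by NH) Cox proportional hazards regression model will be used". It compares seropositive with seronegative participants through a time-varying serostatus, "adjusted for type of participant, history of self-reported SARS-COV-2 infections, and a time-varying NH vaccination degree".

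For the other case the plan gives one sentence: "The analysis will be performed stratified by type of participant or other variables, if the proportional hazard assumption does not hold".

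**The concern.** The objective treats participant type as a comparison to be reported, while the fallback treats it as something to stratify away. Stratification is a sound remedy for a nuisance covariate with non-proportional hazards, because it drops the proportionality assumption for that covariate at the price of not estimating its effect. Here the price is an effect that the objective asks for. If type itself violates the assumption, the resident/staff difference changes over time since vaccination, and the rule then removes the estimate instead of describing the change. The study would reach its report with a listed comparison and no planned number for it. Any substitute would have to be chosen after the data were seen.

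**Working it through.** The plan gives no event count, hazard ratio or power for objective 5, so there is no stated figure to reproduce. The question is whether the contrast can be estimated.

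**Inputs.** The group list, the conditional Cox model and the fallback come from section 3.2, objective 5. The layout of 69 homes, each with 24 residents and 20 staff (69 × 44 = 3036), comes from section 2.5.

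**Step 1, algebra.** Let z be participant type (1 = resident, 0 = staff) with coefficient β, and x the other covariates with coefficients γ. For an event in person i of stratum s at time t, the partial-likelihood term is

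exp(βz_i + γ'x_i) / Σ exp(βz_j + γ'x_j), summed over those at risk in stratum s at t.

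- Strata = homes: a home's risk set can hold both residents and staff, z varies, and β is estimable.
- Strata = homes × type (69 × 2 = 138): z is the same for everyone in the risk set, exp(βz) cancels, and the likelihood does not involve β. The same cancellation occurs if type alone is the stratifier.
- Separate models for residents and for staff, the other meaning of stratified: z is constant in each model, so again there is no β.

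**Step 2, numerical check.** Data were simulated on the protocol's layout. The following are assumptions for illustration: a hazard ratio of 0.5 for serostatus and for previous infection, and a resident/staff hazard ratio of 1 up to day 120 and of 1, 2 or 4 afterwards. Each row averages five simulated data sets.

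| Assumed ratio after day 120 | Home strata: resident/staff HR | Home × type strata: resident/staff HR | Home × type strata: serostatus HR | Home × type strata: previous-infection HR |
|---|---|---|---|---|
| 1 | 1.07 | not estimable | 0.48 | 0.57 |
| 2 | 1.56 | not estimable | 0.46 | 0.51 |
| 4 | 2.60 | not estimable | 0.52 | 0.52 |

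In one further data set with home × type strata, the score and the information for type were both exactly 0. The log partial likelihood was −735.016 at β = −3, at β = 0 and at β = +3. The two other effects stay near their simulated value of 0.5. The zero for type follows from step 1 and does not depend on the assumed rates.

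**Step 3, does another planned analysis supply the contrast?**

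- Primary objective 2 reports sero-incidence for residents and staff separately by two-month period. Its endpoint is antibody conversion, it is not limited to vaccinated participants, and its clock is the study visit. It does not answer objective 5.
- Objective 8 does plan "to model the hazard of SARS-CoV-2 infection between staff and residents, and between vaccinated and non-vaccinated participants". It carries the same proportional-hazards condition and adds non-vaccinated participants to the population. It also has a gate: "If a sufficient number of non-vaccinated participants are available in the sample, a survival analysis will be performed". If too few non-vaccinated residents are available, it is run in staff alone, and the contrast is absent there too.

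**The case against.** The strongest defence is that the model text aims at serostatus. Type enters as an adjustment, and stratifying on an adjustment covariate that violates proportional hazards is standard practice and protects the serostatus estimate. That is right as far as it goes, and the check confirms that the serostatus effect survives. It does not answer the point, because the objective names residents versus staff as a comparison and the fallback names type as the stratifier.

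A second defence is that the objective asks for risk and does not name a hazard ratio, so type-specific curves from the stratified fit could be compared descriptively. They could, but the plan does not say so. What is lost is the model-based estimate and its interval.

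A third is that details may stand in a statistical analysis plan that is not shown. How proportionality is tested and how results are displayed can be left there. The point here is a rule that the protocol does state and that conflicts with its own objective.

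A reader might infer more: that up to three listed comparisons disappear, because the sentence also allows other variables. The text does not support this. Type is the only stratifier it names. Losing all three would mean stratifying also on the time-varying serostatus that the model is fitted to estimate. If previous infection were the stratifier in place of type, that contrast would be lost instead. Nor do the documents show that proportional hazards will fail for type. They give no data on it, and differing waning or differently timed waves would be conjecture.

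**Conclusion.** The point holds in a limited form. When proportional hazards fails and participant type is chosen as the stratifier, objective 5 has no planned estimate or interval for residents versus staff, and objectives 2 and 8 do not fill the gap. For that contrast the loss is complete, since its information is zero. For the objective as a whole it is partial, since the serostatus and previous-infection effects remain. It is a conditional branch of a secondary objective and does not touch the primary objectives. The conclusion rests on reading stratified either as separate baseline hazards or as separate models by type; both readings give the same result. It needs no assumption about event rates.

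**What to change.** Replace the fallback sentence in section 3.2, objective 5. For the factors that the objective names as comparisons, a departure from proportional hazards should be handled by one estimator that keeps the contrast. A factor-by-time interaction in the home-stratified Cox model, reported as period-specific hazard ratios with intervals, would do. Stratification should be kept for variables not named as comparisons. One named estimator is enough.

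The periods should be few and set to suit the number of events, because only homes with both groups still at risk inform each ratio. As an illustration under the simulation's assumptions, single data sets had 152 to 325 events. Over five periods that is about 30 (152 / 5) to 65 (325 / 5) each. The plan gives no expected count against which to judge this.

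The change is one sentence and needs no new data. Its cost is in the result: several less precise ratios instead of one.

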| Secondary objectives                              | This study was designed late 2020, when COVID-19 vaccines were still in research development. However, on January 5 th , 2021, the vaccination campaign in Belgian NH started. The implementation of vaccines directly impacts the seroprevalence, meaning that some of the secondary objectives were no longer accurate (e.g., assessment of risk factors for infection). Therefore, adjustments were made to the secondary objectives, and tertiary objectives concerning the proportion in the sample that is not vaccinated were added. | 2.1 Objectives
3. Data analysis                                                                |
| Additional questions concerning vaccine hesitancy | In the first test round we observed that 15% of staff in the sample were not vaccinated against COVID-19. Therefore, we aim to explore the reason behind vaccine hesitancy by adding additional questions in the follow-up questionnaire of the following sampling point concerning if and why they hesitated/are hesitating to get vaccinated as a part of the follow-up questionnaire (one-off).                                                                                                                                                     | 2.7.2 Demographic and medical data
6.3 Appendix: questionnaires                                |
| Statistical analysis                              | The statistical analysis plan was adjusted to the changes made in the secondary objectives and addition of tertiary objectives.                                                                                                                                                                                                                                                                                                                                                                                                                        | 3. Data analysis                                                                                  |

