## **2.7 Data Collection**

### **2.7.1 Collection of capillary blood samples and point-of-care test procedures**

The capillary blood samples will be obtained using a lancet to finger prick the middle finger and collect a 1-10 drops of capillary blood. A capillary blood drop will be transferred to the

specimen well of a point-of-care (POC) test (COVID-19 IgG/IgM Rapid Test Cassette, Orient Gene Biotech Co.) using a plastic dropper (delivered with COVID-19 IgG/IgM Rapid Test kit). Two drops (ca. 80 µl) of Orient Gene Biotech sample buffer will be immediately added to the buffer well, with avoidance of air bubbles. If the red colour does not move across the test window or if blood is still present in the specimen well after two minutes, one additional drop of sample buffer should be added into the buffer well. The result should be read in 10 minutes, positive test results may be visible as soon as 2 minutes. The result cannot be interpreted after 15 minutes.

The results of the COVID-19 IgG/IgM Rapid Test Cassette should be interpreted as following:

- **Negative:** The coloured line in the control region (C) changes from blue to red. No line appears in the test line region M or G.
- **Anti-COVID-19 IgM positive:** The coloured line in the control region (C) changes from blue to red and a line appears in the test line M.
- **Anti-COVID-19 IgG positive:** The coloured line in the control region (C) changes from blue to red and a line appears in the test line G.
- **Anti-COVID-19 IgG and IgM positive:** The coloured line in the control region (C) changes from blue to red and a line appears in the test line G and M.
- **Invalid test:** Control line is still completely or partially blue and fails to completely change from blue to red. Insufficient specimen sample or incorrect procedural techniques are the most likely reasons for control line failure. The test should be repeated using a new cassette.

For the study any positive result of IgM or IgG will be considered as a positive result. In case of an invalid test, the test is repeated. When it is still invalid it will be noted as such. Additionally, a few drops of capillary blood will be collected on Dried Blood Spot (DBS) collection cards for (semi-)quantitative analysis of vaccine-induced/infection-induced anti-SARS-CoV-2- specific antibodies as a part of the sub-study performed by Ghent University (details are provided in appendix 6.4).

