for COVID-19 relevant preconditions: cardiovascular diseases, diabetes, hypertension, serious heart, lung or renal diseases, immunosuppressing conditions or medication and any form of active cancer. Furthermore, participants (staff and residents) will be asked if they received a COVID-19 vaccination (date, type of vaccine, number of doses), underwent a PCR-/ antigen-test, the date of this test and the result (if more than one test was performed, the date of the first positive test has to be given) or if COVID-19 was confirmed by a CT-scan, and, if they experienced COVID-19 symptoms and when (date). The COVID-19 symptoms episode will be defined according to the Sciensano case definition:

- At least one of following acute principal symptoms not explained by another clear cause: coughing, dyspnoea, chest pain, sudden loss of olfactory sense and/or taste;

OR

- At least two of following symptoms not explained by another clear cause: fever, myalgia, tiredness, rhinitis symptoms, sore throat, head ache, anorexia, diarrhoea, acute confusion, sudden collapse

OR

- Worsening of chronic respiratory symptoms (COPD, asthma, chronic cough) not explained by another clear cause

Additionally, staff members are asked questions concerning vaccine hesitancy (if and why they hesitated to get vaccinated against COVID-19), see Appendix 6.3.

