For vaccinated NH residents only, a survival analysis will be performed to investigate the proportion of deaths within the study follow-up and the time (in days) to a confirmed COVID-19 death since 14 days after being fully vaccinated (full dose regimen). The survival or censoring time (in days) is registered since 14 days after being fully vaccinated until first event (or censoring moment). A non-COVID-19 related death will be considered as a competing risk in the analysis. If the proportional hazard assumption holds, a stratified (by NH) Cox proportional hazards regression model will be used to model the cause-specific hazards between seropositive and seronegative residents. The latter will be included as a time-varying covariate. A history of self-reported SARS-COV-2 infections, a time-varying NH vaccination degree, province, age, gender, care profile, and presence of COVID-specific comorbidities will be

considered for model adjustment.

7. To assess the duration of SARS-CoV-2 specific antibody response (seroreversion/no antibody response) since 14 days after being fully vaccinated among NH residents and staff in Belgium.

The duration of SARS-CoV-2 specific antibody responses among NH residents and staff in Belgium will be modelled by means of an interval-censored survival analysis. Seroreversion will be defined as a negative rapid test result after at least one positive rapid test result or as two succeeding negative test results (implying the participant did not seroconvert after vaccination within two to four months). The time interval to seroreversion/no response is the time interval between 14 days after the (second) vaccination date (full dose regimen) and the first test moment of a negative test result after at least one positive rapid test or of the two succeeding negative rapid test results. As a sensitivity analysis, the event will also be defined as two succeeding negative rapid test results (whether or not after at least one positive rapid test result), if the rapid test result would turn out to be unstable.

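### Objectives 5 and 6 state no entry rule, so for some participants the survival clock starts before enrolment and before the first serology result

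*Protocol*

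**What the plan says.** Objective numbers are those of Protocol section 3.2.

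- **Time origin.** Objective 5 (infection): "The survival or censoring time (in days) is registered since 14 days after being fully vaccinated (full dose regimen) until first event (or censoring moment". Objective 6 (death of residents): "The survival or censoring time (in days) is registered since 14 days after being fully vaccinated until first event (or censoring moment". Neither says when a participant enters the risk set.
- **Exposure.** Serostatus is time-varying in both. For objective 5 it is "modelled by the inclusion of a time-varying seropositivity status"; for objective 6, "The latter will be included as a time-varying covariate". It comes from the rapid test (section 2.7.1): "For the study any positive result of IgM or IgG will be considered as a positive result". The first value is the month 0 result.
- **Calendar.** The Table of changes gives 5 January 2021 as the day on which "the vaccination campaign in Belgian NH started", and reports that 15% of sampled staff were unvaccinated in the first test round. Table 1 marks the first blood collection in February 2021. Section 2.4 spreads the baseline visits over about four weeks.
- **Enrolment.** Consent is signed no later than the first data collection (section 2.6).
- **Past infections.** For the date of a positive test, section 2.7.2 specifies: "if more than one test was performed, the date of the first positive test has to be given". The baseline forms in Appendix 6.3 likewise ask for one date, that of the first positive PCR or rapid test, with a separate date for a CT-confirmed case.
- **Model.** Both Cox models are stratified by nursing home.

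**The concern.** If a participant passes the origin before the first visit, the days in between count as follow-up although the participant was not yet under study. Three consequences follow.

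1. **Deaths (objective 6).** A resident who died in that stretch could never be sampled. Everyone who contributes the stretch survived it, so it is immortal time.
2. **Serostatus (objective 5).** No rapid test exists in that stretch. If the month 0 result were applied backwards, an infection in the gap could produce the seropositive label with which it is then associated.
3. **History (objective 5).** The baseline form holds a single first-positive test date. A participant who tested positive in 2020 therefore cannot show a second test-dated infection in the gap, while a participant without history can show one. Previous infection is a named contrast of this objective, and the difference arises between people in the same home.

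At stake are the description of mortality after vaccination and two of the comparisons in objective 5.

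**Working it through.** The protocol gives no event count or precision for objectives 5 and 6, so there is no stated figure to reproduce.

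**Step 1: can the clock precede the first visit?** Inputs: campaign start 5 January 2021; 14-day lag; first visits in February, or up to late March if the four-week round starts at the end of February. The dose interval is not in the protocol, so 21, 28 and 84 days are assumed. Earliest origin = 5 January + interval + 14 days. Gap = first visit minus origin, for a home vaccinated on the first campaign day:

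| Interval | Earliest origin | Visit 1 Feb | 15 Feb | 28 Feb | 28 Mar |
|---|---|---|---|---|---|
| 21 d | 9 Feb | -8 | +6 | +19 | +47 |
| 28 d | 16 Feb | -15 | -1 | +12 | +40 |
| 84 d | 13 Apr | -71 | -57 | -44 | -16 |

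Homes vaccinated later have smaller or negative gaps. The gap is real for some participants and absent for others.

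**Step 2: crude death rate in objective 6.** Take 300 days of follow-up and use the resident loss of 0.4 from section 2.5 as an exponential loss.

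- Rate λ = -ln(0.6)/300 = 0.00170 per day.
- Mean time under observation = (1 - 0.6)/λ = 234.9 days.
- Diluted rate / true rate = 234.9/(234.9 + gap).

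| Gap (days) | 7 | 14 | 19 | 28 | 47 |
|---|---|---|---|---|---|
| Ratio | 0.97 | 0.94 | 0.93 | 0.89 | 0.83 |

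These ratios apply to residents who have such a gap, not to the whole cohort.

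**Step 3: hazard ratio in objective 6.** A gap shared by everyone in a home, with no events in it, shifts all times in that stratum equally and leaves the risk sets unchanged. Simulation: 69 homes × 24 residents, true HR 0.50, underlying gaps of 0-47 days, Cox model stratified by home, 200 replicates, Monte Carlo SE about 0.013 on the log scale.

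| Gap pattern | No delayed entry | Delayed entry |
|---|---|---|
| Shared within home | 0.50 | 0.51 |
| Individual, unrelated to serostatus | 0.50 | 0.50 |
| 20 days shorter if seropositive | 0.55 | 0.50 |
| 20 days longer if seropositive | 0.47 | 0.51 |
| 40 days longer if seropositive | 0.42 | 0.51 |

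**Step 4: history contrast in objective 5.** Suppose history has no effect (true HR 1.0) and those with history can record no event in the gap. With a constant hazard, they show events over 300 days of their 300 + gap days, and those without history over all of them. The recorded ratio is about 300/(300 + gap): 300/314 = 0.96, 300/328 = 0.91, 300/347 = 0.86.

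A simulation stratified by home agrees: HR 0.95, 0.91 and 0.87 for gaps of 14, 28 and 47 days, and 1.00, 1.00 and 1.02 with delayed entry. Assumptions: 69 × 44 participants, 40% with history, 15% infected over 300 days, gap shared within a home; Monte Carlo SE about 0.013 on the log scale.

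**The case against.** The strongest reply is that the protocol fixes a time scale and need not fix the risk set. Delayed entry and the handling of a time-varying covariate between tests often sit in a statistical analysis plan, and nothing here says that the month 0 result will be carried back. That is fair for the carry-back, which is therefore a possibility and not a stated error. It does not dispose of the point. The text says from when survival time is registered, and followed literally that counts the gap. Objective 8 also expressly counts positive tests reported at the baseline visit as events.

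Several stronger readings are tempting, and the protocol does not support them:

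- **That most participants have the gap.** This needs a dose interval that the protocol does not give. Section 2.7.2 also foresees homes vaccinated only after baseline.
- **That the gap is risk-free in both objectives.** It is so for deaths only. Dated infections before baseline are collected and can be events in objective 5, so an understated infection rate is not shown.
- **That the main exposure is undefined.** Serostatus is defined in section 2.7.1. It is unknown only before the first test.
- **That reverse causation affects both objectives.** Death cannot precede the sample or create the serostatus label.
- **That the objective 6 hazard ratio is badly biased.** Visits are organised by home, vaccination rounds are recorded by home and the model is stratified by home. Step 3 shows almost no movement unless the gap differs by serostatus within a home, and the protocol gives no reason to expect a particular difference.

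The follow-up forms ask about positive tests in the past two months, so the unequal capture in step 4 is confined to the gap before baseline.

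**Conclusion.** The point holds in limited form. For participants who passed 14 days after full vaccination before their first visit, the stated clock starts before enrolment and before any serology.

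- **Objective 6:** the gap is immortal time. It lowers crude death rates for affected residents by about 3% to 17% (gaps of 7 to 47 days) and shifts the description of time to death. The hazard ratio stratified by home is largely protected.
- **Objective 5:** infections in the gap can be counted without any prior serostatus, so reverse causation is possible and no stated rule prevents it. The history contrast leans towards protection, roughly 0.95 to 0.87 for a true 1.0 at gaps of 14 to 47 days.

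These sizes rest on an assumed 21- or 28-day dose interval, on first visits between February and late March 2021, on the planned 0.4 resident loss for step 2, and on the simulation settings given. With an 84-day interval there is no gap.

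**What to change.** Keep 14 days after full vaccination as the time scale for objectives 5 and 6 and add an entry rule:

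- Each participant enters the risk set at the later of that date and the first valid rapid test (left truncation).
- Serostatus at any event time is taken only from tests done before that time.
- Infections before entry count as history, not as events.

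Objectives 8 and 9 do not use serostatus, so entry there should be at the later of their time origin and the baseline visit. The objective 8 wording that counts positives reported at baseline should be brought into line with this.

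The cost is a short addition to section 3.2, the edit to objective 8, and one start-time variable in the Cox data sets. A few infections before the first visit are lost as events. In the simulations delayed entry returned the true values to within simulation error: 0.50-0.51 for a true 0.50, and 1.00-1.02 for a true 1.0.
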